## Abstract

**Background:**

In England, a national breast screening programme (NHSBSP) has been in place since 1988, and assessment of its impact on breast cancer incidence and mortality is essential to ensure that the programme is indeed doing more good than harm. This article describes large observation studies designed to estimate the effects of the current programme in terms of the benefits on breast cancer incidence and mortality and detrimental effect in terms of overdiagnosis. The case-control design of the cervical screening programme evaluation was highly effective in informing policy on screening intervals and age ranges. We propose innovative selection of cases and controls and gathering of additional variables to address new outcomes of interest and develop new methodologies to control for potential sources of bias.

**Methods/Design:**

Traditional case-control evaluation of breast screening uses women who have died from breast cancer as cases, and women known to be alive at the time of case death as controls. Breast screening histories prior to the cases’ date of first diagnosis are compared. If breast screening is preventing mortality from breast cancer, cases will be characterised by a lesser screening history than controls. All deaths and incident cases of primary breast cancer in England within each 2-year study period will be included in this ongoing evaluation. Cases will be age- and area-matched to controls and variables related to cancer treatment and breast tumour pathology will be obtained to investigate the interplay between screening and treatment, and the effect of screening on incidence of advanced stage disease. Screening attendance at other national screening programmes will also be collected to derive superior adjustment for self-selection bias.

The study is registered and has received full ethics approval.

## Background

Breast cancer is the most commonly diagnosed cancer among women in the UK, accounting for a third of all female cancer cases, and the second most common cause of cancer death: in England in 2010, the age-standardised rate per 100,000 women-years was 125.7 for incidence and 24.3 for mortality; in addition, in situ breast cancer, that is Ductal Carcinoma In Situ (DCIS) and Lobular Carcinoma In Situ (LCIS), was diagnosed at a rate of 18 per 100,000 women in 2010 (CRUK, Accessed 28 March 2013 [1]).

In the early nineties, meta-analyses of the randomised controlled trials (RCTs) confirmed the efficacy of mammographic screening for reducing primary breast cancer mortality, and led to the implementation of breast screening programmes in several regions of Europe. One of the most mature and comprehensive of those is the English National Breast Screening Programme (NHSBSP) which has been in place in England since 1988. A major issue to be addressed by the Department of Health’s (England) Policy Research Unit in Cancer Awareness, Screening and Early Diagnosis (PRU), is to evaluate the policy of mammography screening as delivered in the current NHSBSP in terms of benefits on mortality from and on incidence of invasive primary breast cancer, and harms from the most adverse outcome of breast screening. Overdiagnosis is the detection of a breast cancer that would never have been clinically identified in the lifetime of the woman if she had not been screened. In the post-RCT epoch, analytical observational studies are the design of choice.


Data from demographic and cohort population studies were recently used to provide estimates of overdiagnosis in the service screening setting: in England and Wales, overdiagnosis was estimated to be between 3.3 and 10% of the expected cumulative incidence from age 50 to 79 in the absence of screening after correction for self-selection bias and lead-time bias (Paci et al., 2012 [7]). Evaluation on a large scale is needed to confirm those bias corrections.

Mortality from breast cancer has been declining in the UK population since the early 1990s (CRUK, Accessed 28 March 2013 [1]). This fact coincides with the introduction of both the national screening programme, and new adjuvant therapies, and the respective role of those two factors in mortality reduction is a matter of debate (Cancer Intervention Surveillance Modelling Network (CISNET) Breast Cancer Collaborators, 2006 [8]).

In view of the above, there is a need for a large case–control study to (1) evaluate the effect of the NHSBSP on primary breast cancer mortality, with improvements to design and analysis methodology for coping with bias, notably self-selection bias: we propose to do this by developing a procedure using data from different cancer screening programmes. In addition, there is a need to (2) quantify the relative contributions of screening attendance, tumour attributes and treatment variables on case fatality in primary breast cancer, (3) assess the effect of screening attendance on primary breast cancer incidence, (4) estimate the rate of overdiagnosis due to screening, and (5) estimate the effect of screening attendance on incidence of advanced stage primary breast cancer. This final check may firstly give a result earlier than mortality and therefore confer greater statistical power, and secondly be used as a check on the mortality result. Inconsistency between the observed effect on mortality and that on advanced stage disease will indicate that further work is required to deal with residual bias.

Meeting the above aims will entail retrieving more information than in the traditional case–control evaluation of screening. It will include live incident cases as well as dead ones, and diseased controls as well as disease-free ones. Additional variables such as cancer treatment, breast tumour pathology, and screening attendance at other national screening programmes will also be collected.

This will be an ongoing biennial evaluation to ensure that the programme continues to deliver the anticipated health benefit, and to potentially improve the programme by identifying good and bad practices.

## Methods/Design

### Study design & objectives

This study is comprised of two sets of retrospective matched case–control studies: the first set involves dead cases of primary breast cancer (cases A), and the second set, recently diagnosed (or incident) cases of primary breast cancer, dead or alive (Cases C). The dead cases will be matched with two different sets of controls: two general population controls who were alive at the case’s date of death (Controls B), and one diseased control who was alive at the case’s date of death and had had invasive primary breast cancer (screen-detected, interval and never screened will all be included) at the case’s date of first diagnosis (Controls E). The incident cases will be matched to two controls from the general population (Controls D). Subsets of cases and matched controls will be selected for the purpose of each case–control evaluation objective (see *Participants*: *Selection of cases & controls* for details).

**
*Case–control study 1 (CC1)*
** will be a matched comparison of the breast cancer dead cases (A) with the general population controls (B) with respect to screening exposure strictly prior to the case’s date of first diagnosis (set as pseudo-diagnosis date in controls). There will be two controls per case. This design should allow the evaluation of screening exposure modalities in relation to mortality from breast cancer.

**
*Case–control study 2 (CC2)*
** will be a matched comparison of the breast cancer dead cases (A) with the diseased controls (E) with respect to screening exposure strictly prior to the case’s date of first diagnosis (set as pseudo-diagnosis date in controls). There will be one control per case. This design should enable assessment of the interplay between screening attendance, tumour attributes and treatment variables on fatality from breast cancer.

**
*Case–control study 3a (CC3a - Incidence)*
** will be a matched comparison of recently diagnosed/incident **invasive** breast cancer cases (C) with the general population controls (D) free of invasive disease with respect to screening exposure strictly prior to the case’s date of index diagnosis (set as pseudo-diagnosis date in controls). There will be one or two controls per case. This design should allow the evaluation of screening attendance in relation to breast cancer incidence.

**
*Case–control study 3b (CC3b - Overdiagnosis)*
** will be a matched comparison of recently diagnosed/incident invasive and in situ breast cancer cases (C) with the general population controls (D) **free of invasive** and of **invasive or in situ** disease, respectively, with respect to screening exposure strictly prior to the case’s date of **index** diagnosis (set as pseudo-diagnosis date in controls), and will be stratified by age at diagnosis/pseudo-diagnosis. There will be one or two controls per case. This design should allow the evaluation of overdiagnosis due to screening attendance.

**
*Case–control study 4 (CC4)*
** will be a matched comparison of recently diagnosed/incident **advanced stage** breast cancer cases (C) with the general population controls (D) free of advanced stage disease with respect to screening exposure strictly prior to the case’s date of **index** diagnosis (set as pseudo-diagnosis date in controls). There will be one or two controls per case. This design should allow the evaluation of screening attendance on incidence of advanced stage breast cancer. In principle, one should include all advanced breast cancers as cases, i.e. whether advanced at diagnosis or whether subsequently progressed to advanced; however, in practice it will not be possible to identify those that subsequently progress. This analysis will be compared to the analysis of fatal breast cancers to see whether advanced breast cancer can be used as a surrogate endpoint when studying the impact of breast screening on breast cancer mortality.

An overview of the proposed case–control studies and corresponding populations are presented in Figure 1.

**Figure 1 F1:**
[figure not shown]
**Overview of the case–control study designs.** Legend: Thick circles, cases; Thin circles, controls; Full border, individuals with cancers; Dotted border, general population individuals, most of whom have not had cancer, but may have had DCIS or Early Stage Cancer^2^). ^ Match on date of birth within 1 month either side; 2 controls per case. * Match on date of birth within 1 month either side; 1 control per case. # Match on date of birth within 1 month either side, date of first diagnosis within 2 months prior to *and including* the case’s date of first diagnosis; 1 control per case. ^1^Advanced stage is defined as lymph node positive or tumour size >20 mm or both. ^2^Early stage is defined as lymph node negative, and tumour size ≤20 mm.

### Setting & source population

The background, implementation and organisation of the NHSBSP are described in detail elsewhere (Advisory Committee on Breast Cancer Screening, 2006 [9]). For this study, all women who were invited to participate in the breast screening programme in England (from 1988 onwards), and who did not express dissent to their records being used for evaluation purposes, will be targeted.

The evaluation will begin with a pilot phase in collaboration with the Knowledge & Intelligence team London, KIT London (formerly Thames Cancer Registry), using cases that died from or were diagnosed with breast cancer between 1st of January 2008 and 31 of December 2009 in London. The main phase of the study will then be undertaken, which will cover the whole of England or, in the case of CC2, those regions (i.e. previous cancer registries) for which tumour attributes and treatment variables will be available from 1st of January 2010 - in collaboration with the Office for National Statistics (ONS). Each main phase evaluation will cover a 2-year period.

### Participants: selection of cases & controls

#### **
*CC1 & CC2*
**

*Population of dead cases (A)* All women who died of primary breast cancer (as stated in part 1 of the death certificate) age 47–89, within the specified 2-year study period will be selected. Cases of women with only in situ primary breast cancer records (i.e. no invasive record) will be included, but Death Certificate Only (DCO) cases will be excluded. Case A women will have had their date of first diagnosis of primary breast cancer (in situ or invasive) age 47–89 and since 1990, and for subsequent phases of this evaluation (main phase onwards), they will not have been included as cases in previous evaluation periods, although they may have been included as controls, and may also be selected as a case C in the same evaluation.

*Population of cases A-matched general population controls (B)* For each case A, two women will be selected among the general population in the Health & Social Care Information Centre (HSCIC) database at Exeter who, are registered in the same National Health Applications and Infrastructure Services (NHAIS) system as the case at the case’s date of first diagnosis, are alive at the case’s date of death, and were born within 1 month either side of the case’s date of birth. Control B women may have had primary breast cancer (in situ or invasive) at the case’s date of first diagnosis. For subsequent phases of this evaluation (main phase onwards), they will not have been included as population controls B, E, or D in previous evaluation periods, although they may be included as a controls E or D within the same evaluation period.

*Population of cases A-matched diseased controls (E)* For each case A, one woman will be selected among the CR population who was alive at the case’s date of death, and was born within 1 month either side of the case’s date of birth. DCO cases will be excluded. Control E women will have had primary invasive breast cancer diagnosed within 2 months prior to *and including* the case’s date of first diagnosis and: this is necessary to ensure that the control survived for at least as long as the cases. She will have been registered in the same Cancer Network (CN) at the case’s date of first diagnosis. If no control E is found using this criterion, the date range will be expanded to 3 months prior to the case’s date of first diagnosis (or 6 months prior, if the case’s age at first diagnosis is less than 50 or over 70). For subsequent phases of this evaluation (main phase onwards), they may have been included as population controls B or D in previous or within the same evaluation periods, and may be included as a case C within the same evaluation period.

#### **
*CC3a, CC3b & CC4*
**

*Population of incident cases (C)* All women who have had primary breast cancer (in situ or invasive), diagnosed age 47–89 within the specified 2-year study period will be selected. The **index diagnosis** will be either a first or a subsequent tumour and, therefore, women may have had a previous history of in situ or invasive primary breast cancer (i.e. prior to the date of their index diagnosis). Case C women may have died from primary breast cancer (as stated in part 1 of death certificate) age 47–89 during the specified 2-year study period, or afterwards. Cases of women with in situ primary breast cancer records only (i.e. no invasive record) will be included, but DCO cases will be excluded. For subsequent phases of this evaluation (main phase onwards), they will not have been included as cases in previous evaluation periods, although they may have been included as controls, and may also be selected as a case A in the same evaluation.

*Population of cases C-matched general population controls (D)* For each case C, two women will be selected from the general population in the HSCIC database at Exeter who, are registered in the same NHAIS system as the case at the case’s date of index diagnosis, are alive at case’s date of index diagnosis, and were born within 1 month either side of the case’s date of birth. For subsequent phases of this evaluation (main phase onwards), they will not have been included as population controls B, E, or D in previous evaluation periods, although they may be included as controls B or E within the same evaluation period.

Incident cases (C) and matched general population controls (D) will be selected *a posteriori* by the PRU, using tumour information, to suit the purpose of each case-study (see Figure 1).

**For CC3a**, incident cases (C) will be restricted to those women with invasive breast cancer, and matched general population controls (D) will be restricted to those women who have never had invasive primary breast cancer, but may have had in situ primary breast cancer prior to *and including* the case’s date of index diagnosis.

**For CC3b**, all incident cases (C) will be selected. For in situ cases, matched general population controls (D) will be restricted to those women who never had primary breast cancer (in situ or invasive) prior to *and including* the case’s date of index diagnosis; for invasive cases, to those women who never had invasive primary breast cancer, but may have had in situ primary breast cancer.

**For CC4**, incident cases (C) will be restricted to those women with advanced stage (defined below) primary breast cancer, and matched general population controls (D) will be restricted to those women who have never had advanced stage primary breast cancer, but may have had in situ or early stage primary breast cancer prior to *and including* the case’s date of index diagnosis. Breast cancer will be defined as “advanced stage” if tumour size is larger than 20 mm, or if at least one regional lymph node is affected, or if both, and as “early stage” if tumour size is equal to or smaller than 20 mm and no regional lymph node is affected. For the purpose of data collection, we have used an inclusive definition of “advanced stage”, but we will also analyse the data by Stage to assess the association between screening and metastatic breast cancer for instance, and using only those cases which are node positive, as this is generally accepted as an important prognostic factor and as a predictor of the effect of screening on mortality (Smith et al., 2004 [10]).

If no matched control is found for a particular case (A or C) with a date of birth within 1 month either side of the case’s date of birth, the range will be expanded to 3 months either side (or 6 months either side if the case’s age at index diagnosis of primary breast cancer is under 50 or over 70).

All cases and controls will appear on the HSCIC database at Exeter. We will aim to select female cases and controls who have been registered with the NHS by age 47 (determined by either date of first registration on local NHAIS system or prior cervical/bowel screening history), and have had available data on both breast and cervical (for women aged 47–64), and, possibly bowel (for women aged 60–69) screening strictly prior to their date of first diagnosis/pseudo-diagnosis (that is, they have been invited to screening at least once), although this may not be practicably feasible for dead cases and matching controls with older age at death. Patient breast, cervical, and bowel (for the main phase) screening history, primary breast tumours attributes and treatment data will be retrieved for all cases and controls, as well as deprivation quintile.

A detailed description of the algorithm to be used for the selection of cases and controls is available from the authors.

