Applying a restriction on the date of diagnosis during the selection of dead cases can also introduce a form of lead-time bias. Among cases who died from breast cancer on the same date, the screen-detected ones would have received their diagnosis earlier than the symptomatically-diagnosed cases, and therefore would tend to be excluded during the selection, introducing a bias in *favour of screening*. No restriction on the case’s date of diagnosis will be applied at the design stage, i.e. all women diagnosed after the inception of the NHSBSP, i.e. since 1990, will be included in the study.

#### **
*Length bias*
**

Length-biased sampling occurs when the chance of an observation being in a sample is proportional to a particular characteristic of the observation. In the context of screening, length bias is the phenomenon whereby slower-growing, less aggressive tumours (including DCIS) have a longer pre-clinical screen-detectable period (PCDP) and are therefore more likely to be screen-detected compared to faster-growing, more aggressive cancers. This will confer a bias *in favour of screening*, which will be addressed at the analysis stage of case-study 2 by performing sensitivity analyses. Two latent tumour populations will be assumed, one – the “length bias group” - with both a higher probability of being screen-detected and a correspondingly lower probability of fatality, whether actually detected by screening or symptomatic (Duffy et al., 2008b [19]).

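### As written, the re-use rule for dead cases removes deaths among women who were incident cases in an earlier period, so the CC1 and CC2 case sets depend on diagnosis date and change from period to period

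*Protocol article*

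**What the plan says.** Under Participants: selection of cases & controls, the paragraph on dead cases (A) opens by selecting "All women who died of primary breast cancer (as stated in part 1 of the death certificate") at age 47-89 within the two-year period. For the main phase onwards it adds that "they will not have been included as cases in previous evaluation periods, although they may have been included as controls". The word for cases carries no letter. The only overlap with incident cases that it permits is within one evaluation: "and may also be selected as a case C in the same evaluation".

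The paragraph on incident cases (C) takes all women diagnosed at age 47-89 in the period. It notes that they may die of breast cancer "during the specified 2-year study period, or afterwards".

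Two other places state the intended scope of the dead cases. The Abstract says "All deaths and incident cases of primary breast cancer in England within each 2-year study period will be included in this ongoing evaluation". The Lead-time bias part of Bias & Effect modification warns that "Applying a restriction on the date of diagnosis during the selection of dead cases can also introduce a form of lead-time bias" and concludes that "all women diagnosed after the inception of the NHSBSP, i.e. since 1990, will be included in the study".

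The paragraph on controls B bars women who were controls B, E or D in an earlier period. It does not bar earlier cases C, and it allows a control B to have had breast cancer.

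**The concern.** Every woman diagnosed in an evaluated period is a case C of that period. If she dies of the disease in a later period, the clause bars her from being a case A, so her death enters neither CC1 nor CC2. An earlier case C who survives is not barred from being a control B. The same history thus excludes a woman as a case but not as a control.

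The protocol plans a repeated biennial evaluation to confirm continuing benefit. If the composition of the dead cases shifts with each round because of a bookkeeping rule, a change in the odds ratio between rounds could be read as a change in the programme. Epoch of diagnosis is also a planned effect modifier and a CC2 stratifier. In evaluated epochs, the only deaths left would be those in the same two-year window as the diagnosis.

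**Working it through.** **1. Whom the clause can remove.** An earlier case is either an A or a C. An earlier A is already dead, so only an earlier C can be affected. By date of diagnosis, a death in a given main period is:
- kept if the diagnosis dates from 1990 up to the start of the evaluation;
- removed if the woman was a case C in an earlier evaluated period;
- kept if the diagnosis falls in the same window as the death.

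This is a restriction by date of diagnosis, which the Lead-time bias text says will not be applied.

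**2. First main phase.** The only earlier period is the London pilot of 2008-2009 (Setting & source population), with at least 1400 cases C (Study size / Power calculation). Assume that 2-8% of these die of breast cancer in the next two years, and take the protocol's circa 18,000 cases per two years as deaths.
- 1400 × 0.02 = 28 and 1400 × 0.08 = 112.
- 28/18,000 = 0.2% and 112/18,000 = 0.6%.
- If all London incident cases were used, and London is assumed to be 10-15% of England, the loss is 1.2-3.9% under the hazards in step 4.

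**3. Later periods, simple model.** Assume death is uniform in the two-year window and time from diagnosis to death among fatal cases is exponential with mean m years. Ignore the pilot and the 1990 limit. With k earlier national periods:
- share diagnosed in the same window = 1 − (m/2)(1 − e^(−2/m));
- share removed = (1 − e^(−2k/m)) × (m/2)(1 − e^(−2/m)).

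| | m = 4 | m = 8 |
|---|---|---|
| Same window | 21% | 12% |
| Removed, second main period (k = 1) | 0.393 × 0.787 = 31% | 0.221 × 0.885 = 20% |
| Removed, third (k = 2) | 0.632 × 0.787 = 50% | 0.393 × 0.885 = 35% |

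**4. Later periods, alternative model.** This uses constant incidence, diagnoses since 1990 and other-cause mortality of 1.5% a year. Four breast cancer death hazards were assumed: 1% a year; 2% a year; 3% for five years then 1.5%; and 4% for five years then 1%. Earlier national cases C account for 11-25% of deaths in the second main period, 20-44% in the third and 34-53% in the fifth. Together the two models give 11-31% in the second and 20-50% in the third.

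**5. Power.** At an odds ratio of 0.7, power stays above 99.9% even with 6,000 dead cases. The loss of numbers does not matter.

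**6. Direction of the selection.** In the model of step 3, the women removed in the second main period have mean survival 2[m − 2/(e^(2/m) − 1)], which is 1.8 years for m = 4 and 1.9 years for m = 8. The mean among kept deaths is (m − removed share × that mean)/(1 − removed share):
- m = 4: (4 − 0.310 × 1.83)/0.690 = 5.0 years, against 4.0 unselected;
- m = 8: (8 − 0.196 × 1.92)/0.804 = 9.5 years, against 8.0 unselected.

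Early on, the kept deaths are therefore longer survivors on average. By the sixth main period (k = 5) the picture depends on m. With m = 4, same-window deaths make up 77% of those kept and median survival is 0.7 years, against 2.8 unselected. With m = 8, they make up 31% and mean survival is 13.2 years, against 8.0.

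A simulation with 30% of fatal cases screen-detected and mean lead time of 2 or 4 years (all assumed) shows the same drift. The odds of being screen-detected among kept deaths, relative to all deaths, are about 1.1-1.2 in the second main period and about 0.4-1.0 by the ninth.

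**The case against.** The strongest reply is that the unlettered word means cases of the type being defined. The clause then says only that a woman is not a case A twice, which is harmless. That reading agrees with the paragraph's opening sentence and with the Lead-time bias text. The article also says that a detailed selection algorithm is available from the authors. This has weight: the operative rule may differ from the printed one. But the reading leaves the clause with nothing to do, the control rules name letters where a type is meant, and the permission for A/C overlap is limited to the same evaluation. If cases A alone were meant, the sentence still needs correcting.

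The Abstract is weaker evidence than the body text, since the eligibility criteria already narrow its claim (age, date of first diagnosis, death-certificate-only cases). The contradictions within the case A paragraph and with the Lead-time bias text do not depend on it.

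A reader might infer that the rule cripples the mortality study. The documents do not support that: the first national evaluation loses at most about 4% of deaths, and power is ample throughout.

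A reader might also infer a fixed bias in favour of screening through over-inclusion of short survivors, because the Background raises that for earlier regional studies. Those studies kept only recent diagnoses, and the remark there is itself hedged. This rule also keeps old diagnoses, and step 6 shows that the kept deaths are at first longer survivors. No bias in an odds ratio has been computed here.

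**Conclusion.** The clause is wrong as written. Followed literally, it yields a set of dead cases that contradicts the protocol's own definition and its stated refusal to restrict by diagnosis date, and it treats cases and controls B differently. The consequence is negligible in the first main phase (about 0.2-4% of deaths) and substantial from the second (roughly 11-31%, then 20-50% in the third).

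These percentages rest on assumed survival curves, on assumed shares for London and on reading circa 18,000 as deaths. They also assume the literal rule is the one applied. The logical point in step 1 needs none of the numerical assumptions. The damage is to comparability between biennial evaluations, through a selection that drifts and can change direction.

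**What to change.** In the paragraph on dead cases (A), state that earlier inclusion as a case C does not bar selection as a case A, or limit the exclusion to women not previously included as a case A. Either wording keeps every otherwise eligible death in the period. Check that the detailed selection algorithm says the same before the second main period is selected.

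The cost is one sentence. Some women will be a case C in one period and a case A in a later one, an overlap already accepted within a period, and the planned conditional logistic regression is unchanged.

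The same sentence appears for cases C, where it affects women with a later second tumour. That is secondary and has not been quantified, but the wording should be clarified at the same time.
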